**Objectives and brief methods:**

Our primary objective is to evaluate the TtLIVE intervention compared to a usual care control group using an eight-center, pragmatic, parallel-group single-blind (outcome assessors) randomized controlled trial. Eligible patients are children and adults newly transitioning to HMV in Ontario, Canada. Our target sample size is 440 participants (220 each arm). Our co-primary outcomes are a number of emergency department (ED) visits in the 12 months after randomization and change in family caregiver (FC) reported Pearlin Mastery Scale score from baseline to 12 months. Secondary outcomes also measured in the 12 months post randomization include healthcare utilization measured using a hybrid Ambulatory Home Care Record (AHCR-hybrid), FC burden using the Zarit Burden Interview, and health-related quality of life using the EQ-5D. In addition, we will conduct a cost-utility analysis over a 1-year time horizon and measure process outcomes including healthcare provider time using the Care Coordination Measurement Tool. We will use qualitative interviews in a subset of study participants to understand acceptability, barriers, and facilitators to the TtLIVE intervention. We will administer the Family Experiences with Care Coordination (FECC) to interview participants. We will use Poisson regression for a number of ED visits at 12 months. We will use linear regression for the Pearlin Mastery scale score at 12 months. We will adjust for the baseline score to estimate the effect of the intervention on the primary outcomes. Analysis of secondary outcomes will employ regression, causal, and linear mixed modeling. Primary analysis will follow intention-to-treat principles. We have Research Ethics Board approval from SickKids, Children’s Hospital Eastern Ontario, McMaster Children’s Hospital, Children’s Hospital-London Health Sciences, Sunnybrook Hospital, London Health Sciences, West Park Healthcare Centre, and Ottawa Hospital.

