### Sample size {14}

To determine our sample size we used simulations and data from our previous study of VAIs using Ontario health administrative data [2]. We simulated data based on a negative binomial distribution assuming 50% of VAIs visit the ED and had a mean number of 2.6 visits, for an overall yearly incidence rate of 1.3 ED visits. We need 200 participants/ study group to detect a 30% drop-in yearly incidence rate to of 0.91 at 12 months with *α* = 5% and power 80%. Given an estimated attrition rate of 10%, we will recruit a total of 440 participants. For our co-primary outcome, assuming a minimum clinically important difference in the Pearlin Mastery Scale score of 2.95, standard deviation of 4.5, power of 90%, and alpha = 5%, we would require a sample size of 50 study participants in each group for a total of 100 participants [38, 39]. Therefore, with our planned sample size of 440 participants, we are powered for our co-primary outcomes of ED visits and family caregiver reported Pearlin Mastery Scale score.

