### Recruitment and patient consent {15}

There are approximately 1200 new ventilators (100/month) across Ontario/year. We are aiming to recruit a conservative 20% (*n*=20) of all new ventilator users/month. Study participants will be recruited from 8 different HMV programs across the province of Ontario. These HMV programs chosen prescribe over 85% of all ventilators in the province. Study recruitment will occur over a 22-month period. The clinical teams from each of the HMV programs will introduce the study.

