We anticipate challenges associated with our trial delivery. First, bi-monthly data collection via telephone may be burdensome for ventilator-assisted individuals and caregivers already dealing with complex health issues. However, our group has demonstrated success in engaging ventilator-assisted individuals and their caregivers using similar data collection methods in the past [6]. Burden will be minimized by flexibility in terms of call scheduling. Second, there is a risk of increased loss to follow-up in the control group because of fewer clinical interactions. To aid retention, the control group will have monthly telephone calls for completion of the AHCR-adapted providing an active opportunity to promote ongoing participant engagement. Third, as with many trials, we anticipate challenges with maintaining recruitment targets. We have actively engaged with our participating sites with bimonthly team meetings throughout the study setup. These meetings will continue throughout the trial to facilitate discussion and input from team members regarding ongoing project conduct, troubleshooting, and strategies to optimize recruitment success. We have included a 3-month recruitment target ramp-up period from trial launch to allow study sites to become proficient with the study procedures. We are also providing tablets with SIM cards to study participants without a smart device and/or reliable internet access to overcome this barrier to participation.

In summary, this trial of a virtual transition intervention for individuals going home with new HMV will provide important data to understand the effects on healthcare utilization, patient and family experience, health system costs, and healthcare provider time due to increased care efficiency. We anticipate our findings will have applicability for the provision of community-based supports for the HMV population in other regions as well as other high-needs populations in the healthcare system.

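### The 10% attrition allowance is added on (400 × 1.10) instead of divided out (400/0.90), so 440 recruited leaves 198 per arm, just short of the 200 stated as needed

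*Protocol article*

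**What the plan says.** **Sample size {14}.** For ED visits the requirement is: "We need 200 participants/ study group to detect a 30% drop-in yearly incidence rate to of 0.91 at 12 months", with 5% alpha and 80% power. The allowance for loss follows: "Given an estimated attrition rate of 10%, we will recruit a total of 440 participants". The Abstract gives the same total as 220 per arm. The section concludes that 440 is enough for both co-primary outcomes. The caregiver mastery outcome needs only 50 per arm, from a "minimum clinically important difference in the Pearlin Mastery Scale score of 2.95, standard deviation of 4.5, power of 90%, and alpha = 5"%.

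**Recruitment and patient consent {15}.** The aim is 20 participants a month, described as 20% of the roughly 100 new ventilator users a month in Ontario. "Study recruitment will occur over a 22-month period".

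**Discussion.** "We have included a 3-month recruitment target ramp-up period from trial launch". No rate is given for those three months.

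**Trial status.** Recruitment began on 16 March 2021 and is estimated to finish by 1 February 2023.

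**Outcomes {12} and the missing-data section {20c}.** ED visits are taken from health administrative data as well as the participant-completed record. Follow-up shortened by death is handled with an offset for its duration.

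**The concern.** The section states a requirement (200 per arm), a loss rate (10%) and a recruitment total (440), and the third does not follow from the first two. Adding 10% to the requirement is not the same as recruiting enough that the requirement survives a 10% loss, because the loss applies to the larger, recruited number. The ED outcome sets the sample size, so the shortfall falls there; the mastery outcome has a wide margin.

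The accrual figures raise a smaller question of the same kind. The monthly target times the recruitment period gives 440 exactly, which leaves no slower months at that rate, although a slower start is said to be built in. What is at stake there is how far the estimated completion date can be relied on.

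**Working it through.** **1. Reproducing the stated total**

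Inputs from Sample size {14}: 200 per arm, so 400 in all; 10% attrition.

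- 400 × (1 + 0.10) = 440. This is exactly the stated figure.
- Dividing instead: 400/(1 − 0.10) = 444.4, so 445, or 446 with equal arms (200/0.90 = 222.2, so 223 per arm).
- What 440 leaves: 440 × 0.90 = 396, or 198 per arm. That is 2 per arm (1%) below 200.

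**2. Effect on power for ED visits**

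Inputs from the same section: yearly rates 1.3 and 0.91, rate ratio 0.70, alpha 5% (taken as two-sided, which the section does not state). The dispersion used in the simulation is not given. The section's 80% at 200 per arm is therefore accepted and the negative binomial dispersion *k* solved to match it.

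- Variance of the log rate ratio = (1/1.3 + *k* + 1/0.91 + *k*)/*n*, with *n* per arm.
- Power = Φ(|ln 0.70|/SE − 1.96), with |ln 0.70| = 0.357.
- Setting power to 80% at *n* = 200 gives *k* = 0.69.
- At *n* = 198, power = 79.6%, a loss of about 0.4 percentage points.

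The size of the drop hardly depends on *k*. At *k* = 1.66, where a plain negative binomial with mean 1.3 has 50% zeros, going from 200 to 198 per arm also costs about 0.4 points. The level of power at other dispersions is a separate question and is not judged here.

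**3. Mastery outcome**

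2 × (1.96 + 1.2816)² × (4.5/2.95)² = 48.9, so 49 per arm against the stated 50, which reproduces. At 198 per arm its power exceeds 99.9%.

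**4. Accrual**

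- 20 × 22 = 440, with every month at full rate.
- 16 March 2021 to 1 February 2023 is 687 days; 687/30.4375 = 22.57 months. At a flat 20 a month that is about 451, a margin of about 11 over 440.
- Three full-rate months are worth 60. A margin of 11.4 allows a ramp-up averaging (60 − 11.4)/60 = 81% of full rate before 440 is missed at the stated date.

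The ramp-up rate is not stated, so three patterns are assumed. The months after the ramp-up number 22.57 − 3 = 19.57.

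| Assumed first 3 months | Recruited in ramp-up | Monthly rate then needed for 440 by 1 February 2023 | Months to 440 at 20 a month |
|---|---|---|---|
| 1/3, 2/3, full rate | 40 | (440 − 40)/19.57 = 20.4 | 3 + 400/20 = 23.0 |
| Half rate on average | 30 | (440 − 30)/19.57 = 21.0 | 3 + 410/20 = 23.5 |
| No accrual | 0 | 440/19.57 = 22.5 | 3 + 440/20 = 25.0 |

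Against 22.57 months, completion at 20 a month would come about 0.4, 0.9 or 2.4 months after the stated date.

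**The case against.** **The attrition slip is too small to matter.** It is 2 per arm on a round number that came from simulation. The 10% may also overstate the loss for this outcome: someone who stops completing questionnaires can still contribute ED visits through linked administrative data, and someone who dies contributes time at risk through the offset. This stands as to size, and it is why no larger target is asked for. It does not remove the slip, because the protocol itself applies the 10% to the ED calculation and its total should follow from its own inputs.

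**The accrual figures are not strictly incompatible.** The monthly figure is an aim and may be an average over the period. The ramp-up rate is unstated, the dates allow slightly more than 22 months, and a journal article may leave the accrual projection to the full protocol. This largely stands. What remains is that the published figures, read together, do not show where the ramp-up sits.

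**Stronger readings a reader might infer.** One is that 440 can be reached only if there is no ramp-up. The documents do not support it: about 20.4 to 21 a month afterwards reaches 440 by the stated date under the first two patterns above. Another is that a slow start would cut the analysed number and cost several points of power. That needs recruitment to close on a date whatever the count, and no section says so; 440 is the target and the end date is an estimate. A third is that the 20% share is wrong because only the participating programs recruit. The recruitment section defines the share over all new users in Ontario, and 20 out of 100 is correct on that definition.

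**Conclusion.** The point holds as a small arithmetic error in Sample size {14}. With 10% attrition, 440 recruited yields 396, or 198 per arm, and not the 200 per arm stated as needed. Power for ED visits is then about 79.6% where 80% is stated. This rests on accepting 80% at 200 per arm, a two-sided 5% test and a full 10% loss of ED data; if less is lost, the shortfall shrinks. The mastery outcome is unaffected.

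The accrual part is a minor inconsistency of presentation between the recruitment section, the Discussion and Trial status. Its possible consequence is a completion date later by about two weeks to two and a half months, depending on an unstated ramp-up rate. It changes neither the target of 440 nor its power.

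**What to change.** In Sample size {14}, state that 440 recruited with 10% attrition leaves about 198 per arm, with power just under 80% for ED visits. A total of 446 would preserve 200 per arm exactly, but the gain does not call for a larger target. The cost is one sentence.

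In Recruitment and patient consent {15}, give the ramp-up rate and show it in the accrual projection, so that this section, the Discussion and Trial status agree. On an assumed half-rate ramp-up, for example, that means either about 21 a month afterwards over the 22.6 months between the stated dates, or about 23.5 months at 20 a month with the end date moved to match. The cost is wording and, if the rate is kept at 20, about one more month of recruitment beyond the stated date on that assumption.

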### Recruitment and patient consent {15}

There are approximately 1200 new ventilators (100/month) across Ontario/year. We are aiming to recruit a conservative 20% (*n*=20) of all new ventilator users/month. Study participants will be recruited from 8 different HMV programs across the province of Ontario. These HMV programs chosen prescribe over 85% of all ventilators in the province. Study recruitment will occur over a 22-month period. The clinical teams from each of the HMV programs will introduce the study.

### Consent or assent {26a}

Potential participants will be introduced to the study by a physician or clinic team member from the participating sites during a clinic appointment, hospital admission, or other patient encounters when HMV prescription occurs. The physician/HMV team member will review the study participant information sheet with the individual and family member. Interested and eligible individuals will be contacted by the unblinded research coordinator (MA) via email or telephone within 0–2 months of HMV initiation to obtain written informed consent.

{26b}

Additional consents for biological specimens are not necessary.

## Assignment of interventions: allocation

### Sequence generation {16a}

Participants will be randomized to the intervention or usual care arms using a centralized randomization schedule through the Ontario Child Health Support Unit (OCHSU). Randomization will be stratified per site. Randomly permuted blocks of size 6 will be used to ensure that the two groups have similar size throughout the trial for each site as well as for the trial overall. We will use a 1:1 allocation ratio stratified by pediatric, adult amyotrophic lateral sclerosis (ALS) patients, adult non-ALS patients, and type of ventilation (invasive or non-invasive).

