## Assignment of interventions: blinding

### Who will be blinded {17a}

Due to the nature of the intervention, it is not possible for study participants or treating HMV teams to be blinded. The Research coordinator responsible for collecting self-reported outcome measures will be blinded to the allocation assignment. The data analyst will be blinded.

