### Procedure for unblinding if necessary {17b}

The design is open label with only outcome assessors being blinded so unblinding will not occur.

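### A single, published block size of 6 within strata of an open-label trial lets about 22–24% of allocations be deduced in advance, chiefly by the unblinded central coordinator

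*Protocol article*

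**What the plan says.** Sequence generation {16a} in the protocol article fixes one block size: "Randomly permuted blocks of size 6 will be used". It states the strata in two separate sentences: "Randomization will be stratified per site", and "We will use a 1:1 allocation ratio stratified by pediatric, adult amyotrophic lateral sclerosis (ALS) patients, adult non-ALS patients, and type of ventilation". It mentions neither varying block sizes nor keeping the size from those who recruit.

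The design is open: "The design is open label with only outcome assessors being blinded so unblinding will not occur". For those delivering care, Who will be blinded {17a} says "it is not possible for study participants or treating HMV teams to be blinded".

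Two groups control entry to the trial:

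- **Site teams.** Recruitment and patient consent {15} says "The clinical teams from each of the HMV programs will introduce the study", and Consent or assent {26a} says the same of a physician or clinic team member.
- **The central coordinator.** Consent or assent {26a} says "Interested and eligible individuals will be contacted by the unblinded research coordinator", for the purpose of obtaining consent. Implementation {16c} has the coordinator, identified as the same person, enrol and assign participants.

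The only safeguard given, in Allocation concealment mechanism {16b}, is that the central schedule sits inside the REDCap database. Trial status gives recruitment as begun on March 16, 2021 and estimated to finish by February 1, 2023, so the block size was published while recruitment was open.

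**The concern.** Concealment has two parts: nobody should be able to read the list, and nobody should be able to work out the next entry from past ones. A central schedule secures the first. With one known block size it does not secure the second, because the last places in a block follow from those already filled.

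This matters where the people who decide on approach, contact or timing also know earlier allocations. Here the coordinator does, for every stratum. If the next arm can be deduced before a person is contacted, contact can be made, delayed or omitted in the light of it. Both co-primary outcomes, ED visits and caregiver mastery, plausibly depend on who enters each arm. Selection at entry is not repaired by blinded assessors or a blinded analyst, and covariate adjustment corrects only for what was measured.

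**Working it through.** The document gives no predictability figure, so there is none to reproduce. What follows is derived from its design.

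**Inputs.** Block size 6 at 1:1, so 3:3 ({16a}). Total 440 (Sample size {14}). Eight sites, four adult and four pediatric (Study setting {9}). If all factors are crossed and each site enrols only its own age group, there are 4 × 2 + 4 × 2 × 2 = 24 strata. If blocks run within site only, there are 8. The text does not settle which, so both are shown.

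**Certain allocations in a complete block.** There are C(6,3) = 20 orderings. An allocation is certain once one arm has used its three places.

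| Position | 1 | 2 | 3 | 4 | 5 | 6 | Sum |
|---|---|---|---|---|---|---|---|
| Chance it is certain | 0 | 0 | 0 | 1/10 | 2/5 | 1 | 1.5 |
| Chance a best guess is right | 0.5 | 0.6 | 0.6 | 0.7 | 0.7 | 1 | 4.1 |

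- Certain: 1.5/6 = 25%. The general form, 2m/(m+1) per block of 2m, gives 6/4 = 1.5 at m = 3.
- Best guess right: 4.1/6 = 68.3%, against 50% if allocation were unpredictable.

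**Unfinished last blocks.** Take the number of places filled in a stratum's last block as equally likely to be 0 to 5.

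- Certain allocations in that part-block average (0 + 0 + 0 + 0 + 0.1 + 0.5)/6 = 0.1.
- At 25%, its mean 2.5 places would have given 0.625. The loss is 0.525 per stratum.
- 8 strata: 110 − 8 × 0.525 = 105.8, which is 24.0% of 440.
- 24 strata: 110 − 24 × 0.525 = 97.4, which is 22.1% of 440.

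Simulation with 440 participants agrees: 24.0% for 8 strata, and 22.1% (equal sizes) or 22.3% (unequal sizes) for 24.

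**With block sizes drawn at random from 4, 6 and 8.**

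- *Guesser knows the set of sizes but not each block's size.* By simulation with 18 participants per stratum, about 2.4% of allocations are certain and the best guess is right about 67% of the time.
- *Guesser also knows where every block starts.* An allocation is then certain only after one arm has taken four places, which can happen only in a block of 8. That gives 2 × 4/5 = 1.6 certain allocations per 4 + 6 + 8 = 18, or 8.9%. This is an upper bound.

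**The case against.** A reader might infer that a quarter of allocations are known before consent, or that each site team sees the full allocation history of its strata. The document supports neither. *Deducible* is the right word, since someone must keep track of the order in a stratum, and nothing says that anyone does. Section {17a} says that treating teams cannot be blinded; it does not say that they see the order of randomisation. Site staff introduce the study around HMV prescription, and consent and assignment follow centrally, within 0–2 months of initiation. Another patient in the same stratum may be randomised in between. Foreknowledge at introduction is therefore weak, and the main exposure lies with the coordinator. These points stand.

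Room to manipulate timing is also limited. At 20 recruits a month over 24 strata, each stratum gains 20/24 = 0.83 a month, so a block takes 6/0.83 = 7.2 months, while eligibility requires initiation within 2 months. This stands for holding a patient back, but not for selective non-contact. The trial expects to enrol about 20% of new users, so a missed approach would not stand out.

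ED visits draw partly on administrative data, and the mastery analysis adjusts for baseline score. These help against biased reporting and measured imbalance, but not against selection on unmeasured features.

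Finally, varying the block size barely changes the best-guess rate (68.3% to about 67%). That is true; the gain is confined to certainty.

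**Conclusion.** The point holds as a matter of exposure. With blocks fixed at 6, about 22–24% of allocations, roughly 97 to 106 of 440, could be deduced by someone following allocation order within strata. The unblinded central coordinator is the clearest case, with site teams a lesser one. The REDCap schedule does not prevent this.

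The range rests on 8 to 24 strata, full recruitment and complete tracking of order; 25% applies only if every block is completed. A reader might go further and conclude that the trial's groups are biased. The document does not support that: it shows an opportunity, no evidence of its use, and no basis for estimating an effect on either co-primary outcome. It also does not show whether sites knew the block size before publication, or how many allocations then remained. This is a cheap improvement to concealment, not a fault that invalidates the design.

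**What to change.** For allocations not yet made, have the randomisation unit issue new lists with randomly varying block sizes, for example 4, 6 and 8, starting at each stratum's next block. Withhold the sizes from the coordinator and the sites. In {16a}, state only that block sizes vary at random.

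The cost is a new set of lists and a short amendment. Imbalance within the smallest strata could be slightly larger. Blocks already open would run out under the old list, so their tails stay deducible. If recruitment has closed, the change has no effect.

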### Allocation concealment mechanism {16b}

The centralized randomization schedule is embedded into the REDCap study database. When a patient is enrolled, they are assigned to an intervention within the database.

### Implementation {16c}

The allocation sequence is generated using a centralized randomized schedule through the Ontario Child Health Support Unit (OCHSU). The centralized research coordinator (MA) will enroll patients and assign participants to interventions based on the centralized randomization schedule results.

